**【Lab Tests】 :**

☞Blood routine: leukocytes, erythrocytes, hemoglobin, erythrocyte pressure product, mean erythrocyte volume, mean hemoglobin volume, mean hemoglobin concentration, platelet count, mean platelet volume, platelet pressure product, neutrophils, lymphocytes, monocytes, eosinophils, basophils, neutrophil absolute value, lymphocyte absolute value, monocyte absolute value, eosinophil absolute value, basophil absolute value, erythrocyte distribution width SD, erythrocyte distribution width CV, large platelet ratio, platelet distribution width.

☞Hemorrhagic and coagulation function: plasma prothrombin time, international normalized ratio of prothrombin time, activated partial thromboplastin time, prothrombin time, plasma fibrinogen.

☞Liver and kidney function: alanine aminotransferase, aspartate aminotransferase, total protein, albumin, globulin, albumin-globulin ratio, total bilirubin, direct bilirubin, indirect bilirubin, alkaline phosphatase, creatinine,  $\gamma$ -glutamine acyltransferase, lactate dehydrogenase, creatine kinase, urea, uric acid, total carbon dioxide, glucose.

☞Inflammatory markers: ultrasensitive C-reactive protein.

☞Infectious disease tests: HBsAg, HBsAb, HBeAg, HBeAb, HBcAb, Anti-HCV, HIVcombin, Anti-TP, CMV-IgM, CMV-IgG.

☞Immunologic tests: IgA, IgG, IgM, total IgE.

☞Pregnancy test: blood beta-HCG, premenopausal female subjects only.

**【Adverse Event Record】**

**【Record of combined medications/treatments】**

**【Imaging】：** CBCT examination.

**【Intraoral photography】：** Photographs were taken to record the condition of the oral cavity and treatment sites.

(6) **Post-treatment follow-up 4:** 6 months ( $D180 \pm 5$  days) after the end of treatment.

**【Periodontal Clinical Indicators】：** Periodontal examination was standardized using the Florida Probe of the Beijing Stomatological Hospital, Capital Medical University. Records: periodontal attachment level AL, periodontal probing depth PD, probing bleeding index BOP, gingival recession GR, tooth mobility TM, and the proposed treatment site (single tooth/subject) were selected by the investigator.

**【Lab Tests】：**

☞ Blood routine: leukocytes, erythrocytes, hemoglobin, erythrocyte pressure product, mean erythrocyte volume, mean hemoglobin volume, mean hemoglobin concentration, platelet count, mean platelet volume, platelet pressure product, neutrophils, lymphocytes, monocytes, eosinophils, basophils, neutrophil absolute value, lymphocyte absolute value, monocyte absolute value, eosinophil absolute value, basophil absolute value, erythrocyte distribution width SD, erythrocyte distribution width CV, large platelet ratio, platelet distribution width.

☞ Hemorrhagic and coagulation function: plasma prothrombin time, international normalized ratio of prothrombin time, activated partial thromboplastin time, prothrombin time, plasma fibrinogen.

☞ Liver and kidney function: alanine aminotransferase, aspartate aminotransferase, total protein, albumin, globulin, albumin-globulin ratio, total bilirubin, direct bilirubin, indirect bilirubin, alkaline phosphatase, creatinine,  $\gamma$ -glutamine acyltransferase, lactate dehydrogenase, creatine kinase, urea, uric acid, total carbon dioxide, glucose.

☞ Inflammatory markers: ultrasensitive C-reactive protein.

☞ Infectious disease tests: HBsAg, HBsAb, HBeAg, HBeAb, HBcAb, Anti-HCV, HIVcombin, Anti-TP, CMV-IgM, CMV-IgG.

☞ Immunologic tests: IgA, IgG, IgM, total IgE.

☞ Pregnancy test: blood beta-HCG, premenopausal female subjects only.

**【Adverse Event Record】**

**【Record of combined medications/treatments】**

**【Imaging】：** CBCT examination.

**【Intraoral photography】：** Photographs were taken to record the condition of the oral cavity and treatment sites.

(7) **Long-term follow-up:** 12 months ( $D360 \pm 5$  days) after the end of treatment.

**【Periodontal Clinical Indicators】：** Periodontal examination was standardized using the Florida Probe of the Beijing Stomatological Hospital, Capital Medical University. Records: periodontal attachment level AL, periodontal probing depth PD, probing bleeding index BOP, gingival recession GR, tooth mobility TM, and the proposed treatment site (single tooth/subject) were selected by the investigator.

**【Lab Tests】：**

☞ Immunologic tests: IgA, IgG, IgM, total IgE.

**【Adverse Event Record】**

**【Record of combined medications/treatments】**

**【Imaging】：** CBCT examination.

**【Intraoral photography】：** Photographs were taken to record the condition of the oral cavity and treatment sites.

## **2. Research institutions and facilities:**

This study recruited subjects from the Department of Periodontics and the Emergency Comprehensive Diagnosis and Treatment Center. There are an ample number of patients with chronic moderate periodontitis available, ensuring an adequate number of eligible subjects who meet the inclusion criteria and do not meet the exclusion criteria can be enrolled. The Department of Periodontics and the Emergency Comprehensive Diagnosis and Treatment Center together have 48 dental chairs, which can provide independent treatment rooms and relatively independent chairs for pre-enrollment discussions with subjects. Additionally, there are enough independent chairs available for post-enrollment oral clinical parameter assessments, periodontal basic treatments, and local injection of hDP-MSC cells.

The release test of the dental pulp mesenchymal stem cell product used in this study conducted by Stomatological Hospital. The items in the release test include: cell count, cell viability. The equipments needed are inverted microscope, sodium chloride injection and trypan blue staining solution. The Stomatological Hospital meets the conditions for release test of dental pulp mesenchymal stem cell product.

After the human dental pulp mesenchymal stem cell preparation is received by the researcher responsible for the management and distribution of stem cell products at the research institution, it will be stored in a portable programmable incubator provided by the preparation institution. The storage conditions require a temperature of 4°C, and the storage time is limited to 10 hours after the preparation of the product. Once the local injection treatment with the stem cell product is completed, the temperature record of the transportation and storage process for the stem cell product will be printed and archived.

The laboratory tests included in the safety assessment indicators of this study will be carried out by the laboratory department. Some of the test items will require blood samples to be sent to an external testing facility for examination. These items include high-sensitivity C-reactive protein, infectious disease testing (cytomegalovirus CMV-IgM, cytomegalovirus CMV-IgG), immunological testing (IgA, IgG, IgM, total IgE), and pregnancy tests. The testing will be conducted after a trilateral agreement is signed between the research institution, the preparation institution, and the external testing facility. The external testing facility is Beijing Edicon Medical Laboratory Co., Ltd., which has obtained ISO 15189 accreditation, CMA metrology certification, and CLIA certification from the CAP, known as the "gold standard" for clinical laboratories. After the completion of the external blood sample testing for this study, Beijing Edicon Medical Laboratory Co., Ltd. will be responsible for the uniform destruction of the samples and will provide periodic destruction certificates to the research institution.

The imaging tests included in the efficacy assessment indicators of this study will be conducted using CBCT measurement, which will be carried out by the radiology department.

## **(7) Participant inclusion and exclusion criteria and group assignment method**

**1. Inclusion criteria:** In order to be included in this study, subjects must meet all of the following criteria:

- (1) Subjects must be between the ages of 18 and 65 years old, and there are no gender restrictions for inclusion in this study;
- (2) Subjects must voluntarily participate in this clinical study and sign an "Informed Consent Form";
- (3) Radiographic examination of the periodontal defect site reveals a wedge-shaped bone defect;

- (4) PD at the periodontal defect site ranges from 4 to 8mm.

**2.Exclusion criteria:** Subjects who meet any of the following criteria will be excluded from this study:

- (1) Subjects with hypertension who have blood pressure readings of systolic blood pressure  $\geq 180\text{mmHg}$  or diastolic blood pressure  $\geq 110\text{mmHg}$  within one month prior to the surgery will be excluded from this study;
- (2) Subjects with systemic diseases such as malignancy (including those with positive tumor screening results), diabetes, heart failure due to heart disease, myocardial infarction within the past six months, angina symptoms within the past six months, or congenital heart disease will be excluded from this study;
- (3) Subjects who have used NSAIDs or corticosteroids within three months prior to the surgery, or those who have been on long-term steroid therapy, or have used bisphosphonate medications, will be excluded from this study;
- (4) Systemic infectious patients;
- (5) Patients with periodontal defects and adjacent periodontal tissues that have received surgical treatment;
- (6) Patients with known allergies to any materials that may be used during the surgical procedure (such as patients with allergy prone constitution or history of allergy to blood products);
- (7) Patients with severe periodontitis (alveolar bone resorption exceeding two-thirds of the root length);
- (8) Patients with severe liver or kidney dysfunction;
- (9) Patients with bleeding tendencies or coagulation disorders (patients with  $\text{WBC} < 3.0 \times 10^9/\text{L}$  or  $\text{PLT} < 60 \times 10^9/\text{L}$ );
- (10) Patients infected with HIV or hepatitis B virus;
- (11) Patients who had unprotected sexual activity within one month prior to screening;
- (12) Pregnant or lactating females or females using female hormone contraceptives;
- (13) Patients who plan to become pregnant themselves or whose partner plans to become pregnant during the study period or within 6 months after study completion;
- (14) Smokers (currently smoking more than 10 cigarettes per day);
- (15) Patients with an expected survival period of less than 12 months;
- (16) Patients deemed unsuitable for participation by the investigators for any other reasons.

**3.Exit/withdrawal criteria:**

- (1) Adverse events occurring during the study period that, according to the investigators, make it impossible to continue with the study;
- (2) Poor compliance of subject with failure to complete follow-ups in a timely manner;
- (3) Use of medications affecting tolerability or safety assessments, such as glucocorticoids, bisphosphonates, estrogens;
- (4) Subjects who consume other substances that may affect tolerance or safety, such as betel nut, or regularly chew tough foods that exert excessive biting forces, such as beef tendon, will be excluded from this study;
- (5) Subject's voluntary withdrawal from the clinical study by expressing their unwillingness to continue to participate to the researcher;
- (6) If a female subject becomes pregnant during the course of the study, she will be discontinued from further participation;

## (7) Attrition.

**4. Translation Assignment Grouping Method:** In this study, a block randomization method was used at each stage, and the randomization was generated by a statistician using SAS 9.4 software. The randomization and grouping coding were implemented in this study. In the first stage, subjects were assigned to either the stem cell treatment group or the saline control group in a 1:1 ratio based on the assigned coding. After completion of this stage, the randomization envelopes were collected by the statistical unit. In the second stage, subjects were assigned to the saline control group, stem cell treatment group, or stem cell re-administration group in a 1:1:1 ratio based on the assigned coding. The statisticians were not involved in the screening, inclusion of subjects, or subsequent clinical research. Throughout the study, the researchers responsible for the safety and efficacy data analysis maintained blinding.

**(8) Required number of cases**

A total of 96 subjects were recruited for this study, divided into three groups: the saline control group, the stem cell treatment group, and the stem cell re-administration group.

The sample size calculation was performed using PASS 16 software. The significance level was set at  $\alpha=0.05$ , and the power of the test was set at  $1-\beta=0.80$ . The research data from the two stages were combined for statistical analysis. Assuming roughly equal sample sizes in the three groups, the sample size calculation was conducted according to the following formula

$$2 \left[ \frac{(t_{1-\alpha/2} + t_{1-\beta}) S}{\delta} \right]^2$$

In the formula, S represents the standard deviation,  $\delta$  represents the effect size (i.e., the difference between the means of the two groups), and n represents the required number of cases per group.

In the first stage of this study, there are two groups, and it is expected to include 46 subjects. They will be randomly assigned in approximately a 1:1 ratio to the stem cell treatment group and the saline control group. In the second stage, there are three groups, and it is expected to include 50 subjects. They will be randomly assigned in a 1:1:3 ratio to the saline control group, the stem cell treatment group, and the stem cell re-administration group.

Based on the information provided, for the two stages of this study, the estimated number of subjects to be included in the saline control group is approximately 33, the estimated number of subjects in the stem cell treatment group is approximately 33, and the estimated number of subjects in the stem cell re-administration group is 30. These numbers fulfill the statistical analysis requirements.

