| Statistical methods      | 
The phases of this study were randomized using block group randomization, with statisticians using SAS 9.4 software to generate random grouping codes. In Phase I, subjects were assigned in a 1:1 ratio according to the code to DPSCs injection group and saline injection group, and the randomization envelopes were recovered by the statistical management unit after the completion of this phase. In phase II, subjects were assigned to the saline injection group, single DPSCs injection group and double DPSCs injection group in a ratio of 1:1:3 according to the phase code. Statisticians were not involved in the screening, inclusion of subjects and subsequent clinical studies. The evaluators of the measurements were kept blinded during the study.
 
Statistical analysis datasets included the full analysis set (FAS), per protocol set (PPS), safety set (SS).
 
Analyses included subject distribution, balance analysis of baseline indicators, efficacy analysis, and safety analysis.
 
Means, standard deviations, medians, quartiles, minimum and maximum values were used for statistical description of measures, and ANOVA was used for comparisons between groups.
 
Statistical descriptions of count and rank information were made using rates or component ratios, and comparisons of count information were made using the <math>\chi^2</math> test or the Fisher exact probability method.
                                                                                                                    |

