#### **(1) Analyzed Population:**

Statistical analysis datasets for the study results included the full analysis dataset (FAS), the protocol compliance dataset (PPS), and the safety Sexuality dataset (SS).

**Full Analysis Set (FAS):** for all cases that had used the study drug after enrollment and had completed at least one efficacy assessment. cases with at least one efficacy assessment completed after enrollment. The estimation of missing values for the main indicators was performed by the method of LOCF (last observation carrying forward).

**Per Protocol Set (PPS):** a subset of the FAS, all cases that comply with the study protocol,

have good compliance, do not use prohibited drugs during the study period, have completed 6 months of clinical observation, and have completed the CRF;

**Safety Set (SS):** all cases that received the study drug after enrollment and had at least one safety assessment. Cases.

In this study, baseline information was analyzed using FAS and PPS analysis. Primary efficacy indicators, secondary efficacy indicators, etc. were analyzed by both FAS and PPS. However, the conclusions obtained from FAS analysis were the main conclusions. When the conclusions from FAS and PPS are consistent, the credibility of the conclusions can be increased.

In the safety analysis, adverse events and adverse reactions, vital signs, and laboratory indicators were analyzed using SS. subjects who were terminated prematurely due to adverse events and various non-therapeutic reasons were included in the safety analysis.

**(2) Statistical analysis plan:** the analysis of the study results included the description of the distribution of subjects, the balance analysis of baseline indicators, the analysis of efficacy, and the analysis of safety.

Mean, standard deviation, median, quartile, minimum and maximum values were used for the statistical description of the measurement data. Comparisons between groups were performed by ANOVA or Kruskal-Wallis rank sum test, and comparisons in groups were performed by paired t-test or Wilcoxon signed rank test. test for within-group comparisons.

Statistical descriptions of counts and rank data used rate or composition ratio, comparisons of count data used  $\chi^2$  test or Fisher's exact probability method, and comparisons of rank data used Kruskal-Wallis rank-sum test.

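### The 0.80 power in section (8) comes from a two-group formula, while the planned between-group test is a three-group ANOVA or Kruskal-Wallis, so the power of the planned test is not established

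*Protocol*

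**What the plan says.** Section (8) combines the data of both stages, sets alpha at 0.05 and power at 0.80, and then writes: "Assuming roughly equal sample sizes in the three groups, the sample size calculation was conducted according to the following formula". The printed expression is 2[(t(1-alpha/2) + t(1-beta))S/delta]², and delta is defined as "the difference between the means of the two groups". No value is given for delta or S, and the section does not say which two of the three groups are meant. It arrives at about 33 saline, 33 single-injection and 30 double-injection subjects and concludes: "These numbers fulfill the statistical analysis requirements".

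The analysis is described in two other places. The Statistical methods row of the scenario summary says "ANOVA was used for comparisons between groups". The statistical analysis plan paragraph of section (XIX) says "Comparisons between groups were performed by ANOVA or Kruskal-Wallis rank sum test". Neither singles out a pair of groups. The primary efficacy measure in section (15) is attachment level AL, evaluated at D90±3.

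**The concern.** A power figure means something only for the test and the alternative it was computed for. Here the figure is for one two-sample comparison at the full 0.05, and the analysis is an overall comparison of three groups. The power of the three-group F-test depends on where all three means lie. The two-group formula does not use the third mean, and the protocol states no pattern of means.

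Two things are at stake. The sponsor cannot say from the protocol how likely the planned test is to succeed. And the overall test does not answer the efficacy question directly: a significant result says that the three means are not all equal, not whether the single or the double regimen differs from saline.

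**Working it through.** **Inputs.** From section (8): two-sided alpha 0.05, power 0.80, group sizes 33 (saline), 33 (single), 30 (double), total 96. Not in the protocol: delta, S, the pair, the pattern of means. These are assumed below and varied. Other sections state the phase II allocation differently; 33/33/30 is used because section (8) rests on it.

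**Step 1: the protocol's own figure.** It cannot be reproduced without delta/S. The formula with normal quantiles shows how strongly it depends on that ratio. For delta/S = 0.70, 2 × [(1.960 + 0.842)/0.70]² = 32.0; with the t correction, 33 per group. For delta/S of 0.5, 0.6, 0.8 and 1.0 it gives 63, 44, 25 and 16 per group. The value consistent with about 33 per group is therefore 0.70, and that is the assumption carried forward.

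**Step 2: two-group power at 0.70 SD** (noncentral t, noncentrality = 0.70 × √(n1·n2/(n1+n2))).
- 33 v 33: noncentrality 2.843, critical t 1.998, power 80.0%.
- 33 v 30: noncentrality 2.775, critical t 2.000, power 78.0%.

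**Step 3: three-group F-test power** at 33/33/30 (noncentral F with 2 and 93 degrees of freedom, critical value 3.094). With SD = 1, λ = Σ nᵢ(μᵢ − μ̄)², where μ̄ is the mean weighted by group size.

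Worked case, means 0, 0.35, 0.70: μ̄ = (33×0 + 33×0.35 + 30×0.70)/96 = 0.339; λ = 33×0.339² + 33×0.011² + 30×0.361² = 7.71; power 68.5%.

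| Means (saline, single, double), in SD | λ | F-test power |
|---|---|---|
| 0, 0, 0.70 | 10.11 | 80.6% |
| 0, 0.35, 0.70 | 7.71 | 68.5% |
| 0, 0.525, 0.70 | 8.50 | 73.0% |
| 0, 0.70, 0.70 | 10.61 | 82.6% |
| 0, 0.70, 1.05 | 18.19 | 97.2% |
| 0, 0.70, 1.40 | 30.82 | 99.9% |

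The first four rows fix the largest difference at 0.70 SD. The last two take 0.70 SD as single v saline and let the second injection add half as much, or as much, again.

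**Step 4: dependence on the assumed ratio.** At 32 per group, delta/S of 0.6 gives 67% for the two-group test and 55% for the F-test with single midway; delta/S of 0.8 gives 89% and 81%. Power for Kruskal-Wallis was not computed; it would also need an assumed shape of distribution.

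**The case against.** Using a two-group formula for the size of each arm and ANOVA as the overall comparison is a common shortcut, and moving to ANOVA does not by itself cost power: with single equal to saline, or single equal to double, the F-test keeps 81% to 83%. The scenario summary classes the study as exploratory. Post-hoc comparisons and their order are commonly left to a statistical analysis plan, which may exist. All of this stands, and it limits the severity. It does not remove the point, because the power claim and the test are both printed in the protocol and refer to different comparisons.

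Three stronger readings are tempting and are not supported.

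- A reader might infer that power drops to about 69% whenever there is a graded dose response. That figure needs delta/S of 0.70, delta read as double v saline, and the single-injection mean midway, close to the least favourable place for it when the largest difference is fixed. The last two rows of the table are also graded responses, and they exceed 97%.
- A reader might infer that the type I error is inflated. Unadjusted pairwise tests at 0.05 would give a family-wise error of about 9% (two tests) or 12% (three), but the protocol plans no such tests. Pairs tested only after a significant F-test gave about 5% in simulation.
- A reader might conclude that testing single v saline first, and double v saline only if that succeeds, is an easy cure. With single midway (0, 0.35, 0.70 SD), single v saline has 29% power. Double v saline behind that gate is reached and significant in about 27% of trials, against 78% when tested alone.

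**Conclusion.** The concern holds in a limited form. The 0.80 in section (8) is not established for the test named in the scenario summary and section (XIX), and the protocol does not give what is needed to work that test's power out. The size of the gap is unknown rather than shown to be large: under the back-solved 0.70 SD and group sizes of 33/33/30, F-test power lies between 68.5% and 83% when 0.70 SD is the largest difference, and at 97% or more when it is the single v saline difference and the second injection adds at least half as much again. All of these figures rest on the assumed 0.70. Separately, and without any assumed effect size, the overall test does not identify which regimen differs from saline. Given the exploratory label, this is a modest point that should be put right, not one that invalidates the design.

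**What to change.** Make the figure and the test agree in section (8), section (XIX) and the Statistical methods row of the scenario summary. Either of two routes will do; both require delta and S to be printed with their source.

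1. **Name one pairwise contrast with saline** for AL at D90 as the primary test at two-sided 0.05, and treat the F-test and the other pair as supportive. The sponsor should choose the pair to which its delta and S refer, and report power at the actual group sizes: at 0.70 SD, about 80% for 33 v 33 (single v saline) or 78% for 33 v 30 (double v saline).
2. **Keep the F-test as primary**, and replace 0.80 with the F-test's own power under a stated delta, S and pattern of three means.

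The cost is wording in three places and one short calculation; neither route adds subjects or procedures. The downside is that the restated power may fall below 0.80, and under the first route only one comparison is primary.
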